#### 2.6.2. Control Groups (CGs)

The THR and TKR control groups will be requested to follow the usual care. The usual care is defined as the full spectrum of patient care practices in which clinicians have the opportunity to individualize care [37]. In this study, after having completed the rehabilitation treatment after surgery, patients will receive recommendations by surgeons and physiotherapists during follow-up visits on the importance and the appropriate quantity of weekly exercise in accordance with WHO recommendations [23]. Participants to the control group will be monthly contacted to monitor the compliance to the WHO’s recommendations. However, no structured long-term exercise training program will be provided.

### 2.7. Data Collection and Measures

All recruited participants will undergo multidimensional assessments before surgery and, subsequently, after completing the rehabilitation treatment (post-surgery baseline) and, 3 and 6 months later. Measures/records collected in each assessment session is summarized in Table 2 and pertain the following domains: general characteristics (age, gender, body mass index, comorbidity, education, social and professional), QoL, impairments and functional status, lifestyle, and safety. In addition, adherence to the exercise program, home-gym distance, and patient’s satisfaction will be investigated only in the participants of the THR and TKR intervention groups.

#### 2.7.1. General Characteristics

The factors that are considered relevant for the outcome of surgical treatment and/or physical activity programs are: age, gender, comorbidity, body mass index, educational level [38,39,40,41], social status [38,39,40], professional status [38,39,40], and home gym-distance [42], the possibility to reach the gym autonomously or with someone’s help, duration and number of sessions of rehabilitation treatment before and after surgery [43].

#### 2.7.2. Primary Outcome

The primary outcome is QoL’s modification, measured with the SF-36 [44,45,46]. SF-36 is one of the most widely used questionnaires to measure the health-related QoL in total hip and total knee arthroplasty patients [47]. SF-36 is composed of 36 items and is focused on measures of two main domains: physical and mental health. It is a multi-item scale that assesses eight health concepts [44]: (1) limitations in physical activities caused by health problems; (2) limitations in social activities because of physical or emotional problems; (3) limitations in usual role activities because of physical health problems; (4) body pain; (5) general mental health (psychological distress and well-being); (6) limitations in usual role activities because of emotional problems; (7) vitality (energy and fatigue); (8) general health perceptions. Validity and reliability of SF-36 have been previously proved also for the Italian version of the questionnaire [48].

#### 2.7.3. Secondary Outcomes 

Secondary outcomes are measures which may influence QoL.

Impairments, functional and clinical status.

Maximal strength of the lower limbs can be reliably measured with a hand-held dynamometer [49,50,51,52]. It measures the peak isometric force generated from a muscle group. It is widely used to evaluate the strength of knee [49,50,51] and hip muscles [52,53,54] in healthy elderly and people with osteoarthritis.

Hip and knee joints mobility [55] are measured by goniometry. 

The Hand Grip test will be measured by Hydraulic Hand Jamar Dynamometer. This measure has been strongly associated with frailty in the elderly population [56,57].

Pain is measured by visual analogue scale (VAS) [58,59,60]. VAS is a psychometric response scale widely used for measuring subjective characteristics that cannot be directly measured such as pain. It is widely used to measure pain in orthopedic studies.

Time Up and Go is a valid and reliable test used to examine physical performance and lower extremity [61]. It has been used in several clinical trials concerning different conditions [62,63,64], including arthroplasty [65,66,67,68]. It measures the time to stand from a standard chair, walk to a 3 m distance, turn around and return to sit on the same chair.

Single Stance test [69] is a useful tool for estimating standing balance and discriminating from low to high functional ability in individuals of various ages and functional levels. It is reliable, swift and easy to administer. It measures time subjects can balance on one leg up to a maximum of 30 s.

The 30 s Chair-Stand Test [70,71] is a valid and reliable single-item performance test for assessing lower limb function. It is performed by counting the number of stands completed in 30 s with hands crossed on the chest. 

The Harris Hip Score (HHS) [72] is a disease-specific, instrument widely used as outcome measure after THR. The domains covered are pain, function, absence of deformity and ROM. It has been translated and validated in the Italian language [73]. 

The Hip Disability and Osteoarthritis Score (HOOS) was developed in 2003 and showed to be effective in measuring patient-relevant outcomes in osteoarthritis patients even after THR [74]. It is a 39-item self-administered questionnaire with five separate sub-scales: pain, symptoms, stiffness, daily living activities, sport and recreation function, and hip-related quality of life. It has been translated and validated in several languages, including Italian [75].

The American Knee Society Scoring (KSS) [76] is a disease-specific scoring system developed to assess patients’ clinical outcomes and functional ability before and after total knee arthroplasty. Knees are examined for ROM, flexion contractures, extension leg, alignment and stability; functional score rates the patient’s ability to walk and climb stairs.

The Knee Injury and Osteoarthritis Outcome Score (KOOS) is a 42-item self-administered questionnaire that proved to be a reliable and valid instrument for evaluating surgery outcomes physical therapy [77,78] for knee impairments. It assesses five outcomes: pain, symptoms, daily living activities, sport and recreation function, and knee-related QoL. It has been translated and validated in Italian [79].

The Western Ontario and McMasters Universities Osteoarthritis Index (WOMAC) [80,81] is a valid and reliable instrument designed to provide a disease-specific measure for patients with osteoarthritis of hip and knee. It includes 24 items in three dimensions: pain (5 items), function (17 items) and stiffness (2 items). Validity and reliability of the instrument have also been demonstrated for the Italian version [82].

The High-Activity Arthroplasty Score (HAAS) [83,84] is focused on lower limb functions. It was specifically developed to assess functional ability variations after lower limb arthroplasty with particular regard to high functioning individuals. The score is a four-item self-assessment measure covering the four domains of walking, running, stair climbing, and general activities. The Italian version of the instrument has been previously validated [85].

##### Life Style

The Recent Physical Activity Questionnaire (RPAQ) [86] is a self-administered instrument. It is divided into three sections (home activities, activity at work, recreation) during the last four weeks. It has been translated and validated in different languages, including Italian [87]. Weekly activity questionnaires will also be used to monitor the physical activity performed by participants of the intervention group outside the gym and by those of the control group. Each participant will be requested to record the amount (minutes) of moderate/intense activity performed each week.

The PAIR questionnaire for patients’ attitudes toward physical activity is an instrument generated within the PAIR project. It investigates following domains: QoL, practice of physical activity, attitude towards physical activity, function, kinesiophobia.

##### Safety

Adverse clinical events (ACEs) that will occur to participants during the study will be carefully recorded. For the intervention groups, the trainer will record the ACEs occurred during the exercise sessions and outside the gym at the end of each session. In the case of three consecutive absences, the coordinating center will contact the participant by telephone to investigate whether the cause of non-attendance at the gym sessions was an ACE. For participants in control group, the ACEs will be registered by the study staff during follow-up. Based on the records, ACEs will be classified for severity (severe: if the ACE involved hospitalization/access to the emergency room; moderate: if the ACE required the intervention of a doctor and/or modification of the usual pharmacological therapy; mild: if the ACE did not require medical intervention and/or modification of the usual pharmacological therapy), place (home: ACE occurred at home; outside: ACE exercise occurred outside the home; gym: ACE occurred during the exercise session), and apparatus (apparatus/system involved).

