### 2.1. Study Design

The study is a randomized controlled trial. At the moment of the pre-surgery medical check-up, persons will be enrolled. After surgical treatment (THR or TKR) and subsequent rehabilitation treatment, persons will be randomly assigned to an intervention group or a control group. The intervention group will participate in a 6-month exercise program based on the PAIR exercise protocol and will receive educational sessions on the importance of maintaining an active lifestyle after THR or TKR. The control group will follow usual-care and will receive recommendations by surgeons and physiotherapist on the importance of maintaining an active lifestyle after THR or TKR. Six months after surgery, participants of both intervention and control group will be assessed before randomization (post-surgery baseline) and, subsequently, after 3 and 6 months (Figure 1).

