#### 2.6.1. Intervention Groups (IGs)

The intervention groups for THR and TKR will be trained under the direct supervision of a graduate trainer in Sports Science. The protocol aims to reach fitness by improving muscular strength, range of motion (ROM), and muscular elasticity, as well as gait, balance and aerobic capacity. The exercise program is structured in 2 days per week 1 h sessions, and lasts six months. Each session is divided into warm-up, strength, balance, flexibility and cool-down sections. The protocol defines strategies to instruct patients and check the correct and safe execution of the motor tasks for both THR and TKR. 

The exercises are chosen to avoid potentially harmful or painful movements or positions according to the participants’ conditions. For instance, exercises in quadrupedal position are excluded for persons with TKR. Exercises with leg adduction movements and in lateral decubitus positions are excluded for persons with THR. In order to follow the progressive workload adapting criteria, frequency, type, time and duration of the training will be modified based on the functional capacity reached by participants. Only common-use low-cost tools, such as elastic bands, yoga mats, dumbbells and soft dumbbells, are used within the exercise sessions. 

In addition, all persons of the intervention groups will be requested to choose an additional third day of the week to carry out at least one of the following activities: brisk walking, cycling or swimming. The duration of these additional activities will be at least 30 min in order to reach the minimum amount of exercise per week of 150/300 min recommended by WHO [23]. Participants to the intervention group will be monthly request how many hours of additional activities has been done during the last month.

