Primary outcome				
Quality of life				
Short-Form Health Survey (SF-36)	X	X	X	X
Secondary outcomes				
Impairments, functional and clinical status				
Maximal strength of the lower limb	X	X	X	X
Hip and knee mobility	X	X	X	X
Hand Grip test	X	X	X	X
Visual Analogue Score (VAS)-Pain	X	X	X	X
Time Up and GO (TUG)	X	X	X	X
Single Stance test		X	X	X
30 s Chair-Stand Test (30 s-CST)		X	X	X
Harris Hip Score (HHS) *	X	X	X	X
Hip disability and Osteoarthritis Score (HOOS) *	X	X	X	X
The American Knee Society scoring (KSS) **	X	X	X	X
Knee Injury and Osteoarthritis Outcome Score (KOOS) **	X	X	X	X
The Western Ontario and McMasters Universities Osteoarthritis Index (WOMAC)	X	X	X	X
The High-Activity Arthroplasty Score (HAAS)	X	X	X	X
Lifestyle				
Recent Physical Activity Questionnaire (RPAQ)	X	X	X	X
Weekly physical activity logs		During whole exercise intervention		
PAIR questionnaire for patients’ attitudes toward physical activity		X	X	X
Safety				
Adverse clinical events		X	X	X
Adherence to the exercise program				
Adherence to the exercise program (only for the intervention groups)		During whole exercise intervention		
Patients’ satisfaction (only for the intervention groups)				
Questionnaire on satisfaction of the exercise program				X

* for THR only; ** for TKR only.

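### Adverse events are collected by different routes in the two arms, so any between-arm safety statement is confounded by unequal ascertainment

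*Protocol article*

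**What the plan says.** The Safety part of section 2.7.3 sets two routes for recording ACEs. In the intervention groups, "the trainer will record the ACEs occurred during the exercise sessions and outside the gym at the end of each session". There is also a back-up for missed sessions, meant to find out whether an event explains the non-attendance: "In the case of three consecutive absences, the coordinating center will contact the participant by telephone". For controls there is one sentence: "For participants in control group, the ACEs will be registered by the study staff during follow-up". It gives no interval and no prompt.

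The same section grades events by severity, place (home, outside, gym) and body system. A mild event is one that needed neither medical care nor a change in usual drugs. A severe event involved hospitalization or the emergency room.

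Other sections bear on how often participants are reached:

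- Section 2.6.1: "The exercise program is structured in 2 days per week 1 h sessions, and lasts six months".
- Section 2.6.1, monthly request: "Participants to the intervention group will be monthly request how many hours of additional activities" were done.
- Section 2.6.2, monthly contact: "Participants to the control group will be monthly contacted to monitor the compliance" with the WHO activity recommendations.
- Table 2 marks the row "Adverse clinical events" at baseline, 3 and 6 months. The row has no arm restriction, whereas rows for the intervention groups only are labelled as such.

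The end of the Introduction and the start of the Discussion both name safety beside efficacy as what the trial is to evaluate. Section 2.8 names no test for ACEs.

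**The concern.** The arms differ in how often events are recorded, over what recall period, and by whom. A mild event leaves no medical trace by definition, so its capture depends largely on someone raising it while the participant still remembers. Gym events cannot occur in controls, so events at home or outside are where the arms can be compared. Those are also collected at every session in one arm only.

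If the exercise arm shows more events, the trial could not tell whether exercise caused them or closer recording found them. If it shows no excess, the reader could not tell whether the trainer missed some. An analysis plan cannot fully repair this, because events that were never elicited cannot be recovered later.

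**Working it through.** The plan gives no figure to reproduce here. The check counts recording occasions from the stated schedule and then illustrates what the imbalance could do.

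**Step 1: occasions per participant after randomization.** Six months is taken as 26 weeks.

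- Intervention: 2 per week × 26 = 52 at full attendance. For someone who stops attending, the telephone call comes after 3 / 2 = 1.5 weeks of missed sessions.
- Control, visits only: 2 (months 3 and 6). Ratio 52 / 2 = 26.
- Control, if the monthly contacts also capture events: 6 + 2 = 8. Ratio 52 / 8 = 6.5.
- Even at an assumed half attendance, 52 / 2 = 26 sessions against 8 contacts is a ratio of 3.25.

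**Step 2: does another section equalise the arms?** The monthly contacts in sections 2.6.1 and 2.6.2 are described as being about activity. The weekly logs record minutes of activity. Table 2 gives both arms the same two post-randomization visits, but nothing says that a comparison would be limited to events reported there.

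**Step 3: illustration with equal true event rates.** None of these assumptions comes from the document. Events occur at a constant rate, memory of an event halves every *h* weeks, and each event can be captured only at the next contact. With contacts *L* weeks apart, the mean captured fraction is

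c(L, h) = (1 − e^(−λL)) / (λL), with λ = ln 2 / h.

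*L* is 0.5 weeks for twice-weekly sessions, 13 for 3-monthly visits and 26 / 6 = 4.33 for monthly contacts. Example for h = 4: c(0.5) = 0.958 and c(13) = 0.397, so the spurious ratio is 0.958 / 0.397 = 2.41.

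The false-difference columns assume 1 true minor event per participant and 40 per arm (2 groups of 20, section 2.4, with no drop-out applied). Event counts x and y are Poisson with mean 40 × c. A difference is declared when |x − y| / √(x + y) > 1.96, over 20,000 simulated trials.

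| h (weeks) | c(0.5) | c(13) | Ratio, 3-monthly | c(4.33) | Ratio, monthly | False difference, 3-monthly | False difference, monthly |
|---|---|---|---|---|---|---|---|
| 4 | 0.958 | 0.397 | 2.41 | 0.703 | 1.36 | 87.4% | 23.7% |
| 8 | 0.979 | 0.600 | 1.63 | 0.834 | 1.17 | 48.5% | 10.4% |
| 13 | 0.987 | 0.721 | 1.37 | 0.893 | 1.11 | 25.1% | 7.1% |
| 26 | 0.993 | 0.845 | 1.18 | 0.944 | 1.05 | 10.9% | 5.6% |

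Ratios use unrounded fractions. At 0.5 true events per participant, the false-difference range is 7.6% to 60.0% with 3-monthly capture and 5.4% to 14.3% with monthly capture. At 2 events it is 16.5% to 99.3% and 6.1% to 42.4%.

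**Step 4: same interval in both arms.** The expected ratio is 1.00, and the simulated false-difference rate is 4.6% to 5.1%, in line with the nominal 5%.

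**The case against.** The strongest reply is that the document fixes no between-arm comparison of events. Section 2.8 names no such test, the hypothesis in the Introduction concerns quality of life and functional and clinical scores, and a gym category that controls cannot fill suggests a descriptive safety profile. This stands in part: the harm is conditional on a comparison being made. But a randomized trial that declares safety as an aim invites one, even if only by setting two columns of counts side by side.

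Other points on that side also have force:

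- The control wording is loose and does not exclude event recording at the monthly contacts. A reader might infer that the contrast is simply 52 against 2; the text supports that only as the widest case. The narrower reading shrinks the imbalance but does not remove it.
- Fifty-two assumes perfect attendance, and the article says that the trainer records events, not that each participant is questioned at every session.
- Table 2 already provides common visits in both arms, so a comparison on a shared schedule is partly available.
- Session recording is a reasonable part of supervising exercise, so some asymmetry is inherent. That is a reason to keep the log, not to compare it with a different source.

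A reader might also infer that the design is biased against exercise as a matter of fact. The document does not support that certainty: the recorder delivers the programme, knows the allocation and could under-record.

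**Conclusion.** The point holds in a limited form. The article states two non-equivalent ways of collecting ACEs, and no other section makes them equivalent. Any between-arm safety statement drawn from all recorded events is confounded by ascertainment. The problem lies mainly in mild events, and some moderate ones, at home or outside. Severe events depend much less on how often participants are asked. Inflation of the exercise arm is the likely direction, not a certain one; under-recording by the trainer would leave the comparison just as hard to interpret.

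No size follows from the document. The illustrative spurious ratios of about 1.05 to 2.4 rest on an assumed recall half-life of 4 to 26 weeks, full attendance, and whether the monthly contacts count. It is tempting to quote a single figure by assuming that controls report some fraction of events, but that ratio would only restate the assumption. The primary quality-of-life outcome is not touched. The change should be made because safety is a declared aim and the remedy is cheap.

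**What to change.** 1. Add one identical scripted adverse-event question, with one-month recall, to the existing monthly contact in both arms. The same type of staff should ask it in both arms, and not the trainer. Say in the Safety section that these contacts and the 3- and 6-month visits are what is meant by follow-up.
2. Add one analysis rule: base any between-arm comparison of events only on those monthly contacts and the two visits, which Table 2 already marks without arm restriction.
3. Keep the trainer's session log and the call after absences for monitoring. Report events found only there separately, as descriptive data for the intervention arm.

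The cost is about a minute per contact and fewer events in the comparison. One limit remains: intervention participants who have already told the trainer about an event may recall it better a month later, so the scheme reduces the asymmetry rather than guaranteeing its removal.

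### The adverse-event place codes cannot separate events tied to the requested third-day exercise, or appearing after a session, from unrelated events, and the outside code is ambiguous

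*Protocol article*

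**What the plan says.** The Safety part of section 2.7.3 sets a wide scope: "Adverse clinical events (ACEs) that will occur to participants during the study will be carefully recorded". In the intervention groups "the trainer will record the ACEs occurred during the exercise sessions and outside the gym at the end of each session", and three absences in a row prompt a telephone call to find out whether an ACE was the cause. For the other arm, "For participants in control group, the ACEs will be registered by the study staff during follow-up".

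Each event is then classified on three axes: severity, place and apparatus. The place axis begins "place (home: ACE occurred at home" and continues "outside: ACE exercise occurred outside the home; gym: ACE occurred during the exercise session". No axis for relatedness to exercise, or for what the participant was doing at onset, is listed.

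Section 2.6.1 describes two supervised one-hour sessions a week for six months. It then asks all intervention participants to "choose an additional third day of the week to carry out at least one of the following activities: brisk walking, cycling or swimming". On length it says "The duration of these additional activities will be at least 30 min", and it gives the reason as reaching the recommended weekly minimum. No trainer is described for this third day. The Adherence part of section 2.7.3 says the third activity is recorded as well.

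**The concern.** The Introduction and the Discussion both name safety of the programme as something the trial will evaluate. To answer that, one would want to know which events arose in connection with the exercise participants were asked to do. The article sets out a specific scheme for classifying events, so this is not simply a detail left to another document. The scheme records where an event happened, and place is a poor stand-in for activity when part of the requested exercise is done away from the trainer.

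On the plain reading, a fall during the requested cycling gets the same code as a fall while shopping. A joint that swells at home on the evening after a session gets the same code as any domestic mishap. At stake is whether the trial can describe exercise-linked events for everything it asked the intervention groups to do, or only for events that happen in front of the trainer.

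**Working it through.** **1. How much requested exercise lies outside the gym code.** Inputs from section 2.6.1: two sessions of 60 min a week, one further day of at least 30 min, six months (taken as 26 weeks).

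- Weekly minutes at the minimum: 2 × 60 + 30 = 150. This reproduces the lower end of the weekly target in section 2.6.1.
- Share of minutes outside the gym code: 30/150 = 20%. If the third day lasted longer (assumed values), 60 min gives 60/180 = 33% and 90 min gives 90/210 = 43%.
- Share of exercise days: 1/3 = 33%. Over 26 weeks: 2 × 26 = 52 sessions and 1 × 26 = 26 third-day activities, so 26 of 78 days.

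These figures describe exposure only. The article gives no event rates, so no number of misclassified events can be derived.

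**2. What the place codes do with typical events.** The outside definition can be read in two ways: (A) any ACE away from home, or (B) an exercise-related ACE away from home.

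| Event | Reading A | Reading B |
|---|---|---|
| Fall during a supervised session | gym | gym |
| Fall during requested cycling on the road | outside | outside |
| Fall while shopping | outside | no code |
| Injury on an exercise bike at home, used as the third-day activity | home | home |
| Joint swelling at home on the evening after a session | home | home |
| Unrelated fall at home | home | home |

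Under A, the second and third rows cannot be told apart. Under B they can, but an unrelated event away from home then has no place code. Under both readings the last three rows share one code. Severity and apparatus do not help, because neither records activity. Two coders could also code the shopping fall differently.

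The gym code refers to the programme's sessions. Control participants have none, so their exercise events can only be home or outside.

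**3. Whether comparing all ACEs between arms solves it.** Set the two ascertainment rules side by side. Intervention: at the end of each session, up to 52 occasions at full attendance, plus the call after three absences. Control: by study staff during follow-up. Table 2 lists ACEs at the 3- and 6-month assessments after baseline, which would be 2 occasions. Section 2.6.2 also has controls contacted monthly; if ACEs were asked about then, which is not stated, there would be about 6. On either assumption the intervention arm is asked far more often. A raw difference in counts therefore mixes any effect of the programme with the effect of more frequent asking.

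**The case against.** The strongest reply is that coding is not capture. Third-day and after-session events are within scope, because the trainer also records what happened outside the gym. A reader might infer from the codes that such events are lost, or that the programme's harms will be understated. The documents do not support either inference. Understatement would follow only if harm were read from the gym code alone, and neither the Safety text nor section 2.8 says that it will be. More frequent asking in the intervention groups would, if anything, tend to raise their count. This part of the objection stands in full.

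Second, in a randomised trial the natural safety estimate is all ACEs by arm, which needs no attribution. That holds in principle, but it depends on like-for-like ascertainment, which the Safety text does not provide.

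Third, the outside definition contains the word exercise, so gym may not be the only exercise code. That is fair, and it is why the ambiguity is part of the point. Reading B still leaves home-based activity and after-session events unidentified.

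Fourth, section 2.6.1 builds the programme from the two sessions and adds the third day on top, and controls are also advised to exercise. However, the third day is requested of the intervention groups specifically, counts toward their weekly minimum, and is recorded. After-session events concern the sessions themselves in any case. A reader might also cite the Discussion's remarks on replication at home; those concern the low-cost-equipment exercises, so they are not relied on here.

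Finally, an unseen full protocol or event form may hold a relatedness item. That is possible and would largely settle the matter. The point is confined to the three axes the article states.

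**Conclusion.** The point holds in a limited form. The stated classification cannot isolate events during the requested third-day activity, or events that appear after a session, from unrelated events. Its outside code also needs correcting. The requested exercise that falls outside the one clearly exercise-linked code is 1 day in 3 and, at the 30-minute minimum, 20% of weekly minutes.

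Neither the size nor the direction of any bias in the safety result can be derived from the article, and none is claimed. The all-ACE comparison remains useful, but unequal ascertainment keeps it from cleanly replacing a link between event and exercise.

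The conclusion assumes that the three listed axes are the whole scheme and that the third-day activity is unsupervised, since no trainer is mentioned for it. It is an inexpensive improvement to how the trial answers its safety question, not a flaw that invalidates the design.

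**What to change.** - Correct the outside definition so that it has one meaning and every event has a place code.
- Add to the event form, identically in both arms, a field for activity at onset: supervised session, requested third-day activity, other exercise, or not exercising. The first two options apply to the intervention groups only.
- Add a yes/no flag for onset or worsening after exercise within an interval set by the investigators.
- Report exercise-linked events from these items, beside the between-arm comparison of all ACEs, and keep place as descriptive.
- When interpreting the between-arm comparison, state that the arms were asked on different schedules. Asking both arms on a common schedule as well, for instance at the monthly contact already planned for controls, would make it cleaner.

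The form changes cost one or two extra items and need no added visits. The count of exercise-linked events may rise, simply because more of them become identifiable.
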